#### Moderators

The moderating role of *stressful life events* will be assessed using the German-version of the Child and Adolescent Survey of Experiences (CASE-C/P [44]). The questionnaire is filled out by both the parent and child and consists of 38 pleasant or unpleasant events that the child may have experienced in the past 12 months. The CASE demonstrates good test-retest reliability (0.75) und good correlation with an interview-based measure of stressful life events [44].

The moderating role of *parental diagnostic status* (current or previous episode of depression) will be assessed using the DIPS [30] interview conducted at T1.

### Statistical analysis and estimated sample size

Intention-to-treat analyses are planned, such that all families who are randomised are included in the final analyses. We will use t-tests and chi-squared tests to check whether randomisation is successful. Interclass correlations (ICC) will be calculated in order to examine the extent to which values for the various outcome measures correlate between members of the same family. Confounding variables (demographics, parental depressive symptoms, course of parental therapy) will be included in statistical models.

In order to assess the impact of the intervention on the primary outcome (depression diagnosis) logistic regression models will be used to generate Odds Ratios (OR). Survival analysis will also be used to measure whether the time to a diagnosis of depression varies between the two groups [16]. In order to assess the clinical efficacy of the programme, the number of participants needed to treat (NNT) to prevent an incidence of depression will also be calculated.

The statistical analysis of the secondary outcome (child’s psychopathological symptoms) will be performed using multi-level regression, with group (intervention vs control) as the predictor variable.

We will also use regression models to assess the influence of moderating (stressful life events and parental diagnostic status) and mediating (knowledge of depression, coping strategies, parenting style, attributional style) variables.

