More generally, prevention programmes for the children of depressed parents have largely been developed and evaluated in the USA [9,17,19,20], with the exception of a study which evaluated the FTI in Finland [18,26]. One quasi-experimental study conducted in Germany compared the effects of a family-based intervention for the children of parents with a psychiatric disorder (not specifically depression) but only measured effects on life-quality and social support (not symptoms or a diagnosis of depression) [27]. Another quasi-experimental study of a selective prevention programme in Germany (EFFEKT-E) administered an intervention to children aged 4–7 whose mothers (but not fathers) had depression [28].

Here we describe the study protocol (Version 1; February 2014) of an RCT comparing a German-language adaptation of the RHC prevention programme with usual care (no routine intervention) for psychiatrically healthy children with a parent who is depressed. To our knowledge, this is the first RCT of its kind to be conducted in Germany. Given previous findings which suggest that interventions may be more effective when parents are not currently depressed [17], we also include non-depressed parents who have experienced a depressive episode during the child’s lifetime. Although we will include children showing sub-clinical symptoms of depression, they will be excluded if they meet diagnostic criteria for a current or previous episode of a psychiatric disorder, including depression. Our hypothesis is that in comparison to a control group who receive no intervention, participants in the experimental group will show a reduced risk of depression as indexed by i) fewer cases of a depressive episode at 15-month follow-up, and ii) fewer psychopathological symptoms at 9- and 15-month follow-up. We expect these improvements to be associated with improvements in the child’s knowledge of depression, the child’s coping strategies and attributional style, and the parents’ parenting skills. Based on previous studies [9,16,17], we expect children whose parents who are not depressed at baseline to show the greatest benefits from the programme. Since the programme is designed to reduce depression by modifying children’s responses to stress, we expect families who experience more stressful life events during the course of the study to show greater benefit from the intervention than those who experience less.

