### Procedure

When both the child and their parent are interested in taking part and make contact with the study team, they will be informed about the details of the study (and the inclusion/exclusion criteria) over the telephone. If they are suitable and still interested, a separate appointment for a screening session will be made. Here the parent and child will be given an overview of the study (including the fact that their allocation to the experimental/control group will be decided at random) and written informed consent will be taken from both the parent and child. Following a diagnostic (screening) interview, baseline measures of all outcome measures (see below) will be administered. If only one parent attends the screening session, the other parent will nevertheless be asked to complete self-report questionnaires about symptoms of general psychopathology and depression specifically. After the appointment, a decision about the family’s suitability for participation in the study will be made, and if suitable, randomisation will be performed. The screening session will be conducted and analysed by someone trained and experienced in conducting psychiatric assessments but who will not be involved in delivering the intervention to the family. At 6- (T2) and 9-months (T3) after baseline, participants will be asked to complete outcome measure questionnaires by post, telephone or electronically. All participants will be invited back for an appointment at 15-month follow-up where the final outcome assessment (T4) will take place.

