**Table 1 Tab1:** **Measures to assess screening, outcome, mediator and moderator variables**

**Function**	**Measure**	**Instrument**	**T1**	**T2**	**T3**	**T4**
Screening	Diagnostic status (parent)	DIPS [30]; SCID-II [31]	X			
	Diagnostic status (child)	K-DIPS [34]	X			
	IQ (child)	CFT-20-R [35]	X			
	Symptoms of psychopathology and depression (non-participating parent)	SCL-90R [32]; BDI-II [33]	X			
Outcome	Diagnostic status (child)	K-DIPS [34]				X
	Psychopathological symptoms (child)	DIKJ [36]; BDI-II [33]; YSR [39]; CBCL [38]	X	X	X	X
Confounding variables	Demographics (age, gender, education level, family income, marital status, nationality)	Self-report	X			
	Depression severity (parent)	BDI-II [33]; DIPS [30]	X			X
	Course of therapy (type, duration and location; parent)	Self-report	X			X
Mediators	Knowledge of depression (child)	Allgaier et al. [40]	X	X	X	X
	Coping strategies (child)	FEEL-KJ [41]	X	X	X	X
	Parenting style	ESI [42]	X	X	X	X
	Attributional style (child)	ASF-KJ [43]	X	X	X	X
Moderators	Stressful life events (child)	CASE-C/P [44] (child and parent report)				X
	Parental diagnostic status (current vs. previous)	DIPS [30]	X			

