#### Outcome measures

The primary outcome is the presence or absence of a *depressive disorder* in the child at 15-month follow-up (K-DIPS). The secondary outcome of the study is the severity of *psychopathological symptoms* immediately after the intervention (T2; 6-months), at 9-month follow-up (T3) and 15-month follow-up (T4). Self-reported symptoms of depression will be collected using the Depression Inventory for Children and Adolescents (DIKJ; children aged 8–12) [36] and the German-version of the revised Beck Depression Inventory (BDI-II; children aged 13 and over) [33]. Both measures are established measures of depression symptom severity with very good internal consistency (0.92 [36] and 0.90 [37] respectively) and good correlations with other measures of depression in this age-group. More general internal and external symptoms will be collected using the german versions of the Child Behaviour Checklist (CBCL/4-18 [38]; parent-report) and the Youth Self-Report (YSR/11-18 [39]), both standard measures used in previous studies of child and adolescent depression prevention [9]. The CBCL/4-18 assesses both internalizing and externalizing behaviours using 118 items which pertain to the frequency of a given behaviour (scored on a three-point likert scale). The YSR allows the youth themselves to report on the same behaviours described in the CBCL. The CBCL and YSR both have good test-retest reliability and good to very good internal consistency [38,39].

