#### Confounding variables

Age (child), gender (parent and child), education level (parent), family income, marital status, nationality, parental depression severity (BDI-II [33] and DIPS [30]) and parental depression treatment (type, duration and location) will be treated as potentially confounding variables.

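### The covariates stated for the models omit the child's own T1 symptom level, so the primary logistic model forgoes a small, nearly free gain in precision

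*Protocol article*

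**What the plan says.** The primary outcome is the presence or absence of a depressive disorder in the child at 15 months by K-DIPS (Outcome measures). The statistical analysis section says of it: "In order to assess the impact of the intervention on the primary outcome (depression diagnosis) logistic regression models will be used to generate Odds Ratios".

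The covariates appear in three places, which agree:

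- Statistical analysis section: "Confounding variables (demographics, parental depressive symptoms, course of parental therapy) will be included in statistical models".
- Confounding variables section: child's age, gender of parent and child, parental education, income, marital status and nationality, and then "parental depression severity (BDI-II [33] and DIPS [30]) and parental depression treatment (type, duration and location) will be treated as potentially confounding variables".
- The confounder rows of Table 1 carry the same items.

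The child's T1 symptom level is in none of them, although it is collected. At the screening session, before randomisation, "baseline measures of all outcome measures (see below) will be administered" (Procedure). Table 1 marks DIKJ, BDI-II, YSR and CBCL at T1. The Background explains why these scores can vary although no child has a diagnosis at entry: "Although we will include children showing sub-clinical symptoms of depression, they will be excluded if they meet diagnostic criteria" for a current or previous disorder. Randomisation is stratified only by parental diagnostic status (Design).

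**The concern.** Diagnosis has no baseline variation, since every child is free of disorder at T1. The severity of the same condition does vary. Among the variables collected at T1 it is the closest to the primary outcome, yet the stated models carry nationality, marital status and location of parental therapy instead.

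In a randomised trial, adjusting for a prognostic pre-randomisation score raises the power of the treatment comparison at no recruitment cost. What is at stake is that efficiency, in a trial that expects about 21 events. The point concerns the primary diagnosis model only, not the secondary symptom model.

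**Working it through.** **1. Reproduce the plan's figure.** Inputs from the Sample size section: 33% control, 10% intervention, one-sided Fisher exact test, alpha 5%, power 80%. Exact enumeration gives power 79.8% at 45 per group and 80.9% at 46, so 46 per group (92 in total) is confirmed. At the recruitment target of 50 per group, exact Fisher power is 84.1%.

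**2. Events.** 50 × 0.33 + 50 × 0.10 = 16.5 + 5 = 21.5.

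**3. Power of the logistic model with and without a T1 score.** 50 per arm, one child per family, no dropout. The score X is standard normal. The logistic model is P(diagnosis) = expit(a + bX), with b = ln(odds ratio per SD) and a chosen in each arm so that the marginal risks stay at 33% and 10%. The odds ratio per SD is an assumption, because the documents give none.

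| Odds ratio per SD (assumed) | One-sided 5%, likelihood ratio: without → with | Gain (points) | Two-sided 5%, Wald: without → with | Gain (points) |
|---|---|---|---|---|
| 1 (not prognostic) | 89.5% → 89.2% | none | – | – |
| 1.5 | 90.2% → 90.7% | 0.5 | 80.3% → 81.8% | 1.5 |
| 2 | 90.2% → 91.7% | 1.5 | 80.3% → 83.2% | 2.9 |
| 3 | 89.8% → 93.2% | 3.4 | 79.8% → 86.0% | 6.2 |

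(15,000 simulated trials per row; 4,000 in the first, where a difference of 0.3 points is simulation noise.)

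At an odds ratio of 2 per SD, the one-sided gain is worth about 4 families per arm: unadjusted power at 54 per arm is 91.6%.

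**4. The same question with a latent liability.** Here the score is correlated with a normal liability that is cut to give 33% and 10%. Both tests are likelihood-ratio tests.

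| Latent correlation (assumed) | Observed correlation, control arm | Approx. odds ratio per SD | One-sided gain (points) | Two-sided gain (points) |
|---|---|---|---|---|
| 0.20 | 0.16 | 1.4 | 0 to 0.5 | 0.4 |
| 0.30 | 0.23 | 1.7 | 0 to 0.5 | 1.3 |
| 0.40 | 0.31 | 2.1 | 1.5 | 3.2 (82.7% → 85.9%) |
| 0.50 | 0.39 | 2.7 | 2.6 | 4.8 (83.0% → 87.8%) |
| 0.65 | 0.50 | 4.3 | 5.5 | 8.4 (83.4% → 91.8%) |

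The two models agree where they overlap.

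**5. With the stated covariates already in the model.** Ten non-prognostic covariates stand in for the confounder list. One-sided power goes from 88.8% to 90.2% at an odds ratio of 2 per SD and from 88.7% to 91.9% at 3, so the gain survives. The long list has its own cost. With ten covariates plus group there are 21.5 / 11 ≈ 2 events per parameter, and the simulated one-sided 5% test rejected a true null in 6.4% of trials (6.1% with the T1 score added). Without those ten covariates the figures were 4.9% and 5.4%.

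**6. Change of estimand.** The marginal odds ratio is (0.10/0.90) / (0.33/0.67) = 0.226. Conditional on the score it is 0.202 at an odds ratio of 2 per SD and 0.173 at 3.

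**The case against.** **The covariate list may not be closed.** It speaks of potential confounders and of models in general, and an SAP may settle the final set. This carries some weight. But the article itemises the covariates and names the same groups in three places, always without the child's T1 score. That is a stated choice that can be improved, not a silence.

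**The gain may be very small.** This stands. Children with any current or previous disorder are excluded, which cuts off the upper end of the symptom range, and the outcome is 15 months away. Nothing in the documents supports a correlation of 0.3 or more. Below that the one-sided gain is under 1 point.

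**No single self-report depression scale covers the sample.** This also stands. DIKJ is for ages 8–12 and BDI-II from 13, and the YSR starts at 11. The CBCL covers all ages but is parent-reported, in families selected for parental depression. How well either option predicts a K-DIPS diagnosis is unknown.

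**Stronger readings that a reader might infer.**

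- *The trial is short of power, or its sample size is wrong.* It is not: 46 per group reproduces, and at 50 per arm the plan's inputs give 84.1% (Fisher) or about 90% (logistic) against a target of 80%.
- *A chance imbalance in T1 symptoms biases the primary odds ratio.* It does not. With 50 per arm the difference in a standardised score has SD √(2/50) = 0.2, and a 0.4 SD imbalance would shift the odds ratio by a factor of about 2^0.4 = 1.3 at an odds ratio of 2 per SD. But such chance differences are already covered by the nominal error rate under randomisation. Adjustment reduces that noise and removes no bias.
- *The gain is 5 to 8 points.* That takes a two-sided test and a latent correlation of 0.5 to 0.65. The only test level the article states is one-sided 5%.

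**Conclusion.** The point holds as forgone efficiency. The stated covariates omit the collected variable closest to the primary outcome. On the plan's one-sided 5% level, with 33% vs 10% and 50 per arm, adjustment adds about 0 to 3 points to a power of about 90% for latent correlations up to 0.5, and about 5 points at 0.65. Two-sided, the gain is roughly 0 to 5 points, and 8 at 0.65. It is nil if T1 symptoms do not predict onset.

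The correlation is an assumption throughout, and sibling clustering and dropout are not modelled. The omission introduces no bias and leaves the sample size calculation correct. It is best labelled a cheap improvement.

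**What to change.** Pre-specify one T1 child symptom score as a covariate in the primary logistic model, and name it in advance. There are two workable choices:

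- the T1 CBCL internalising score, which is one scale for all ages 8–17 but parent-reported; or
- the T1 DIKJ or BDI-II score, standardised within instrument, which is the child's own report but comes from two scales.

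Let it replace named weaker terms, such as nationality, marital status and location of parental therapy, so that the number of parameters does not grow with about 21 expected events. State that the adjusted odds ratio is conditional on baseline symptoms, and derive the NNT from standardised (marginal) risks of the same model.

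The cost is a sentence or two in the analysis section and no new data. The downsides are that the reported odds ratio becomes conditional and that any missing T1 scores need a simple imputation rule.

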### Sample size

We based our sample size calculation on effect sizes found in previous studies. Based on the results of a similar study which recruited the children of depressed parents and included a treatment as usual control group [16,17], we expected 33% of children in our control group to meet criteria for depression at 15 month follow-up (previous studies report 33% at 9 month follow-up [17] and 48% at 24 month follow-up [16]). Based on a study using the same prevention intervention [9,25], we expected around 10% of the experimental group to meet criteria for an episode of depression at follow-up (Compas and colleagues report 9% at 9 month follow-up [9] and 14% at 24 month follow-up [25]). A one-sided Fischer exact test comparing these proportions (10% vs 33%), with an alpha value of 5% and power of 80%, indicates a necessary sample size of 46 families in each group (N = 92 in total). Our aim is therefore to recruit 100 families, although it should be noted that our calculations are limited, since no previous study has recruited children of depressed parents with no previous psychiatric history themselves, or compared the intervention program we intend to use with a treatment as usual control condition.

## Discussion

Children whose parents have suffered from depression have an elevated risk of developing depression themselves, yet there is little formal support available to such children. An effective preventive intervention for this vulnerable group could convey significant personal, social, and economic gains. Although a promising preventive programme which includes both parents and children, and adopts principles of CBT, shows encouraging results, these are yet to be replicated [9]. This protocol describes an RCT to evaluate whether this intervention can be applied to a German sample to reduce the risk of depression in psychiatrically healthy children whose parents suffer from depression.

One hundred participating families will be randomly allocated to receive either i) the GGA preventive intervention, or ii) no intervention. The intervention is a 12-session group- and family-based cognitive-behavioural programme adapted here for the first time in German. The primary outcome measure will be diagnostic status (depression) at 15-month follow-up and the secondary outcome will be psychopathological symptoms immediately after the intervention, as well as at 9- and 15-month follow-up. We hypothesise that in comparison to usual care, the intervention will be effective in significantly reducing children’s risk of a depressive episode and psychopathological symptoms. We expect these improvements in the experimental group to be associated with improvements in knowledge of depression, the child’s coping strategies and their attributional style, and the parents’ parenting skills. We expect families who experience stressful life events during the course of the study, and families in which the parent is not currently depressed, to show the greatest benefits from the programme.

### Risks and side-effects

Existing studies of preventive interventions for families with a parent who is, or has, suffered from depression, provide no evidence of any associated risks or complications. Despite this low-risk, spontaneously reported side-effects of the intervention will be documented by the study leaders and will be discussed in regular supervision sessions. The detailed diagnostic interview conducted at the beginning of the study will ensure that no parents or children are included in the study who require a different type of treatment. Families are entitled to withdraw participation in the study at any point and do so with no disadvantage. During the study, if depression (or another psychiatric disorder) is recognised or suspected in the child, the child and parents will be informed and be offered the opportunity to receive treatment in the clinic for child and adolescent psychiatry. Parents who receive a diagnosis of depression for the first time during the study period will be encouraged to seek treatment at the clinic for psychiatry. Continued participation in the study is nevertheless possible.

## Abbreviations

ASF-KJ: Attribution style questionnaire for children and adolescents
BDI-II: Beck depression inventory
CASE-C/P: Child and adolescent survey of experiences
CBCL: Child behaviour checklist
CBT: Cognitive-behavioural therapy
CFT 20-R: Culture fair intelligence test
CWD: Coping with depression
DIKJ: Depression inventory for children and adolescents
DIPS: Diagnostic interview for psychiatric disorders
DSM-V: Diagnostic and statistical manual for mental disorders
ESI: Parenting style inventory
FEEL-KJ: Questionnaire for the assessment of emotion regulation in children and adolescents
FTI: Family talk intervention
GGA: Gesund und Glücklich Aufwachsen – *“Grow up healthy and happy”*)
ICC: Inter-class correlations
K-DIPS: Diagnostic interview for psychiatric disorders for children and adolescents
LMU: Ludwig-Maximilians University
NNT: Number needed to treat
RCT: Randomised controlled trial
SPIRIT: Standard protocol items: recommendations for interventional trials
YSR: Youth self-report
